### Materials and equipment

The adjuvant HPV vaccine to be administered is the nonavalent HPV vaccine, which is globally approved and utilized in national immunization programs for children. The nonavalent HPV vaccination is an adjuvant non-infectious recombinant 9-valent vaccine. It is prepared from the highly purified virus-like particles (VLPs) of the major capsid L1 protein from the same four HPV types (6, 11, 16, 18) in the qHPV vaccine Gardasil or Silgard and five additional HPV types (31, 33, 45, 52, 58). It uses the same amorphous aluminum hydroxyphosphate sulfate adjuvant as the qHPV vaccine. The VLPs cannot infect cells, reproduce, or cause disease. The efficacy of L1 VLP vaccines is thought to be mediated by the development of a humoral immune response.

The placebo consists of physiological saline (NaCl) with no active ingredients. Preparation and labeling of the investigational medicinal products will be done according to the relevant GMP guidelines. The labels will be in Dutch for the Dutch centers (according to the CCMO rules) and will be translated into the language of each participating country. Distribution will be organized by the Erasmus MC Pharmacy.

### Detailed procedure

Patients with vulvar lesions are referred to the gynecologist according to their regular care. In the case of vHSIL, a biopsy will be taken for histological examination by a pathologist as part of regular care. At that time, potential participants will receive oral and written study information. In the case of histology-proven vHSIL participants will be invited for the screening visit.

In cases of uncertainty about whether a lesion is primary, residual, or recurrent, we have established an independent board of three experts on vulvar diseases to provide a definitive decision by consensus.

During the screening visit, routine cervical cytology (if not previously taken) and HPV status are obtained, along with visual examinations, including photo documentation to monitor lesion progression or regression.

At the follow-up visits, patients will undergo visual and physical examinations, with a preference for photo documentation of the vulva, to monitor any changes or recurrence of lesions or the development of new lesions. In case of suspicion of recurrence or a new lesion, a biopsy is taken. When it is not feasible to take a new biopsy, but new treatment is initiated, this is also considered a clinical recurrence. Quality-of-life questionnaires and immune response analysis will be performed, adhering to guideline-based care.

Recurrence is defined as any reappearance of vHSIL after six months from the start of treatment, while residual disease is defined as the presence of clinical suspicion and preferable histological conformation of vHSIL within six months from the start of the treatment.

In case of uncertainty regarding the histological diagnosis, an expert gynecological pathologist will review the slides digitally.

### Randomization, stratification, blinding and treatment allocation

Randomization will be performed through the secure web-based interface Castor EDC (Castor Electronic Data Capture available at: https://castoredc.com). Patients will be randomly assigned to either adjuvant HPV vaccination or placebo in a 1:1 ratio. Randomization will be stratified by country of inclusion, treatment group (surgery, laser vaporization, and topical imiquimod), and the first episode of vHSIL versus recurrence. The study team, the local investigator, and the patient are blinded for treatment allocation of the study medication. The allocated medication in the Netherlands will be prepared by the pharmacy at the Erasmus MC and administered to the patient by a designated study team member from Erasmus MC. Study medication will be masked for the administrator of the vaccination and the patient.

### Interventions

Patients eligible for participation will be randomized to either a nonavalent HPV vaccine or a placebo vaccine (physiological salt solution for injections). The follow-up will follow the European College for the Study of Vulval Disease (ECSVD) guideline for vHSIL.

The first vaccination is preferably administered concurrently with treatment initiation (utilizing either surgery, laser vaporization, or topical imiquimod). This window spans four weeks prior to treatment commencement (due to potential logistical considerations regarding surgical scheduling) and four weeks post-treatment initiation. The second vaccination should be administered at least one month after the first vaccination and three months preceding the third vaccination. The third vaccination should be administered at least three months after the second vaccination. All vaccinations must be administered within six months.

### Sample size calculations

The sample size calculations are based on the available evidence, which describes a recurrence rate of 19% versus 32% in favor of HPV vaccination [5]. With a target power of 0.8 and a two-sided alpha of 0.05, we need a total of 498 patients (249 in each arm), including a loss of follow-up and a 20% correction of the supposed different effect in treating the first episode of vHSIL versus the recurrence of vHSIL.

### Data analysis

The primary outcome will assess the relative risk of vHSIL recurrence within 24 months, analyzing the efficacy of adjuvant nonavalent HPV vaccination using logistic regression methods adjusted for country of inclusion, treatment types, and primary versus recurrence vHSIL. A 95% confidence interval will be estimated for the odds ratio, with significance determined by a likelihood ratio test. *P*-values below 0.05 will be considered statistically significant.

Analysis of secondary endpoint(s) Secondary objectives 1, 2, 4, 9, and 10 will be analyzed similarly to the primary endpoint, using logistic regression methods adjusted for the stratification variables: country of inclusion, treatment types, and primary versus recurrence vHSIL. 95% Confidence intervals will be estimated for the odds ratios and significance will be determined using likelihood ratio tests. *P*-values below 0.05 will be considered statistically significant.

Secondary objectives where the effectiveness of vaccination is compared between different patient groups (secondary objectives 3 and 5) will be analyzed using logistic regression methods adjusted for stratification variables. 95% Confidence intervals will be estimated for the odds ratio, and significance will be determined using a likelihood ratio test. *P*-values below 0.05 will be considered statistically significant.

Secondary objective 6 will be analyzed using a linear regression model to determine the difference in log-transformed antibody levels at baseline and after placebo or vaccination and adjusted for stratification variables. The impact of change in antibody levels on the primary endpoint will be analyzed using a logistic regression model adjusted for stratification variables. 95% Confidence interval will be estimated for the coefficients, and significance will be determined using a likelihood ratio test. *P*-values below 0.05 will be considered statistically significant.

Secondary objective 8: Quality of Life will be measured at several time points. They will be assessed with a Euroqol 5D-5L questionnaire. Sexual health will be evaluated using FSFI. The impact of vaccination on these measures over time will be analyzed using linear mixed-effect models, with vaccination status and stratification variables as fixed effects and random intercepts as random effects. Additional random effects will be selected based on likelihood ratio tests. A 95% Confidence interval will be estimated for the coefficients, and significance will be determined using a likelihood ratio test. *P*-values below 0.05 will be considered statistically significant.

Secondary objective 7: Cost-effectiveness will be assessed by calculating the incremental cost-effectiveness ratio (ICER), which is defined as the difference in costs divided by the average change in the effectiveness of the vaccine versus placebo following vHSIL treatment. A Budget impact analysis (BIA) will be performed, in accordance with the principles for good practice for BIA, to address the financial stream of consequences to assess the affordability of offering the vaccine following vHSIL treatment.

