**Methods:**

This is a randomized, double-blind, placebo-controlled study protocol involving 498 women diagnosed with vHSIL. Participants will be randomized to receive either the nonavalent HPV vaccine or a placebo in addition to standard treatment. The primary outcome is the recurrence of vHSIL within 24 months following treatment. Secondary endpoints are treatment effectiveness, immune response, cost-effectiveness, and quality of life. Long-term follow-up examines vaccine effect after 5 and 10 years, along with the occurrence of vulvar malignancies. Relative risk between vaccinated and placebo groups will be evaluated, employing intention-to-treat principles.

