## Background

Annually, approximately 45,240 women globally are affected by vulvar carcinoma, with a yearly mortality of 15.000 [1]. Around one-third of vulvar cancers arise from a precursor caused by high-risk Human Papilloma Virus (hrHPV), called vulvar High-Grade Squamous Intra-Epithelial Lesion (vHSIL). The standardized incidence rate of vHSIL in Europe is estimated to be approximately 3.3 per 100,000 women years. In the Netherlands, an average of 300 women are newly diagnosed with vHSIL annually. Across Europe, there has been a consistent upward trend in vHSIL incidence over the past two decades, mirroring patterns observed in HPV-related malignancies [1]. The peak incidence of these precancerous vulvar lesions typically occurs between the ages of 35 and 40 [2]. Approximately 10% of women diagnosed with vHSIL, despite undergoing treatment, will progress to develop vulvar cancer within ten years after initial diagnosis. Recurrent vHSIL substantially increases the risk of malignancy [2].

Despite available treatments such as surgery, laser vaporization, and topical imiquimod, vHSIL recurrence rates remain high, affecting at least 30% of treated women within two years, regardless of treatment modality [2, 3]. Unfortunately, effective preventive strategies to address vHSIL recurrence are currently absent.

Promising empirical evidence suggests that HPV vaccination could reduce the risk of vHSIL recurrence. A retrospective secondary analysis of pooled data of two RCTs showed a significant reduction of 35% (irrespective of causal HPV type) to 64% (related to vaccine type) for recurrences of vHSIL and low-grade squamous intraepithelial lesion (LSIL) after adjuvant quadrivalent HPV vaccination [4]. Recently, a case-control study was published showing a reduction of 40% in recurrences after quadrivalent HPV vaccination; due to small groups, this reduction was not significant [5]. There is a notable absence of high-quality studies investigating adjuvant nonavalent vaccination, specifically in women treated for vHSIL.

We propose a prospective, double-blind, randomized controlled trial to evaluate the efficacy of adjuvant nonavalent HPV vaccination compared to placebo in reducing recurrence rates among women currently treated for vHSIL. Given that almost all HPV variants linked to vHSIL are covered by the nonavalent vaccine, this trial seeks to provide a novel preventive strategy for vHSIL recurrence [6–9].

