### Study objectives and endpoints

The primary objective is to evaluate the efficacy of adjuvant nonavalent HPV vaccination in women who will undergo treatment for (histologically proven) vHSIL in preventing clinical recurrence of vHSIL up to 24 months.

The second objectives are:The effectiveness (complete remission) after treatment in patients receiving vaccination versus placebo at 6 and 12 months.Complete remission after treatment in patients receiving vaccination versus placebo at 6 and 12 months in primary episode (newly diagnosed) vHSIL versus recurrence.The effectiveness of adjuvant vaccination in different treatments of vHSIL (laser, imiquimod, excision) after 24 months.Additional treatment for vHSIL needed in the study period, and differences between the study groups.The effect of vaccination versus placebo on different hrHPV types (HPV type of primary and recurrence).The difference in immune response to HPV vaccination versus placebo vaccination. (We use HPV antibodies as a surrogate marker for immune response. Peripheral blood mononuclear cells (PBMCs) are bio banked for the possibility to measure in-depth cellular immune response at the molecular level at the end of the trial).Cost-effectiveness (IMTA Medical Consumption Questionnaire (iMCQ) and IMTA Productivity Cost Questionnaire (iPCQ) will be used).Quality of life (measured by Euroqol 5D-5L questionnaire) and sexual health (measured by Female Sexual Function Index, FSFI questionnaire) improved after vaccination compared to placebo.The effect of vaccination versus placebo on CIN/cervical cytology of the uterine Cervix.Long-term follow-up: The difference between HPV vaccination and placebo group in number of recurrences of vHSIL (5 and 10 years) and vulvar malignancies (2,5 and 10 years).

The primary endpoint is a difference in the number and percentage of patients with a clinical recurrence rate of vHSIL between HPV vaccination and placebo up to 24 months post-treatment.

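### The primary effect measure is inconsistent: a relative risk is announced, an interval is fixed only for the odds ratio, and the two differ materially when about 32% of controls recur

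*Protocol article*

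**What the plan says.** Three parts of the protocol article describe the primary effect, each in its own terms.

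- Abstract, Methods: "Relative risk between vaccinated and placebo groups will be evaluated, employing intention-to-treat principles".
- Data analysis, first sentence: "The primary outcome will assess the relative risk of vHSIL recurrence within 24 months". The same sentence gives the method, "using logistic regression methods adjusted for country of inclusion, treatment types, and primary versus recurrence vHSIL". The next sentence fixes what is estimated: "A 95% confidence interval will be estimated for the odds ratio, with significance determined by a likelihood ratio test".
- Study objectives and endpoints: "The primary endpoint is a difference in the number and percentage of patients with a clinical recurrence rate of vHSIL", compared between vaccine and placebo up to 24 months after treatment.

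The article names no step that turns the logistic model into a relative risk.

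On how common the outcome is, the sample size section assumes a "recurrence rate of 19% versus 32% in favor of HPV vaccination", and the background describes recurrence as "affecting at least 30% of treated women within two years, regardless of treatment modality".

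**The concern.** An analysis plan can be silent on detail that belongs in a statistical analysis plan. This text is not silent. It names one measure for the primary outcome and fixes the estimate and interval for another. An analyst cannot follow both sentences without adding a step that the article does not describe.

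The choice would not matter for a rare outcome, where the odds ratio approximates the relative risk. Here about a third of control women are expected to recur, so the approximation fails.

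At stake is the size of the headline effect. The expected results section links a successful trial to guideline and reimbursement work, whose readers will look at how large the reduction is. If the measure is still open when the data are unblinded, it could also be chosen with the results in view.

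**Working it through.** **Inputs.** Recurrence of 19% with vaccine and 32% with control, two-sided alpha 0.05, power 0.8 and 249 women per arm (sample size section). Background control rate of at least 30% within two years (background section).

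**1. Which scale the protocol's own figure is on.** The background reports a 40% reduction in recurrences from the case-control study. The sample size section takes 19% and 32% from the same reference.

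- Relative risk: 0.19 / 0.32 = 0.594, a reduction of 40.6%.
- Odds ratio: (0.19/0.81) / (0.32/0.68) = 0.2346 / 0.4706 = 0.498, a reduction of 50.2%.
- Risk difference: 32% − 19% = 13 percentage points.

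The quoted 40% agrees with the risk scale and not with the odds scale.

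**2. Size of the gap at the planning rates.** 50.2 − 40.6 = about 9.5 percentage points (9.53 before rounding).

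**3. Sensitivity to the control rate.** Hold the relative risk at 0.594 and vary the control rate. The 30% is the background figure, 32% is the planning value, and the other rates are assumptions.

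| Control rate | Odds ratio | Gap, percentage points |
|---|---|---|
| 25% | 0.523 | 7.1 |
| 30% | 0.506 | 8.8 |
| 32% | 0.499 | 9.5 |
| 40% | 0.467 | 12.7 |

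The 0.499 in the 32% row, against 0.498 above, comes from rounding the relative risk to 0.594.

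**4. What the intervals would look like.** As an illustration, take 47/249 against 80/249 recurrences, the whole-number counts nearest 19% and 32%, unadjusted and with no losses.

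- Relative risk 47/80 = 0.59. The standard error of its log is √(1/47 − 1/249 + 1/80 − 1/249) = 0.160, so the 95% interval is 0.43 to 0.80.
- Odds ratio (47/202) / (80/169) = 0.49. The standard error of its log is √(1/47 + 1/202 + 1/80 + 1/169) = 0.211, so the 95% interval is 0.32 to 0.74.

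The same data rule out a reduction smaller than about 20% on one scale and about 26% on the other.

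**5. Effect of adjustment.** The planned odds ratio is conditional on the stratification factors. With one assumed balanced binary covariate of log-odds effect 0.5 to 1.0, and marginal risks held at 19% and 32%, the conditional odds ratio is 0.494 to 0.483. The marginal relative risk stays at 0.594. This is small beside the gap in step 2.

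**6. Whether the sample size depends on the scale.** The usual two-proportion formula (pooled variance under the null, no continuity correction) gives 176 per arm before any allowance. A calculation on the log odds ratio gives (1.960 + 0.842)² × (1/0.2176 + 1/0.1539) / (ln 0.498)² = 180 per arm. Both lie below 249. The article does not state the loss percentage, so 249 cannot be reproduced from stated inputs alone. With an assumed 15% loss and a factor of 1.2, 176 × 1.2 / 0.85 = 248.5, which rounds up to 249. Nothing here shows 498 to be wrong.

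**The case against.** The strongest reply is that the plan labels its interval honestly. It says odds ratio, and nowhere proposes to present that number as a relative risk. The odds ratio is a legitimate measure, and any exaggeration needs a reader's mistake. The primary conclusion rests on the likelihood ratio test, which is the same whichever measure is reported. The endpoint definition also calls for counts and percentages by arm, from which a crude relative risk and risk difference follow directly. Finally, writing odds ratio wherever relative risk now stands would also remove the contradiction.

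Most of this stands, and it limits the point. What remains is that the text announces a relative risk twice, so the misreading is invited. The crude figures also do not supply the adjusted relative risk, and no interval is planned for it.

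A reader might go further in four ways that the article does not support.

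- **The odds ratio inflates the vaccine effect in itself.** It does so only when taken for a relative risk.
- **The test, the type I error or the 498 is compromised.** The mismatch touches none of them.
- **The cost-effectiveness ratio is built on the odds ratio.** The data analysis section defines it as the cost difference over the average change in effectiveness, with no mention of odds.
- **The secondary binary endpoints carry the same contradiction.** For these the section names odds ratios throughout and promises no relative risk.

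The 35% reduction from the pooled trials is also best left out of the sizing. It covers high-grade and low-grade lesions together after quadrivalent vaccine, and comes from a different source than the 32% control rate.

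**Conclusion.** The point holds as an inconsistency in the primary effect measure. Three scales appear for one outcome, and the announced measure has no planned adjusted estimate or interval. At the protocol's own rates the relative risk is 0.594 and the odds ratio 0.498, so the same result reads as a 41% reduction in risk or a 50% reduction in odds. The gap is 7 to 13 percentage points for assumed control rates of 25% to 40%. These sizes rest on the planning rates, or on holding their relative risk fixed, and would shrink if the true effect were smaller. At a 32% control rate and a relative risk of 0.8, for example, the odds ratio is 0.731 and the gap 6.9 points.

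The defect concerns the reported estimate and its interval, not the validity of the test or the size of the trial. It should be fixed, but it does not threaten the trial's ability to answer its question.

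**What to change.** Keep the stratification-adjusted logistic model and its likelihood ratio test. From the fitted model, predict each randomised woman's recurrence risk under vaccine and under placebo, using her own stratification factors, and average each set over all randomised women. The ratio of the two averages is the marginal relative risk and their difference is the risk difference. Give both a 95% interval by the delta method or the bootstrap. The stratification factors are known for every woman at randomisation, so the averaging fits the intention-to-treat principle in the abstract.

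Report the relative risk as the primary measure and the adjusted odds ratio as supporting. Word the abstract, the endpoint definition and the data analysis section to match. Calling the measure an odds ratio throughout would also be consistent, but it would drop the measure the article announces.

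The cost is one post-estimation step, a sentence in the analysis plan and a less striking headline figure. No extra data are needed. The change should be made before unblinding.

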### Data collection

All data will be collected using an electronic Case Report Form (eCRF) and electronic questionnaires. Data from the eCRF and questionnaires will be collected and stored using Castor EDC. Sequential subject numbers will be assigned to enrolled participants in the study. Access to stored data will be restricted solely to the principal and coordinating investigators of each participating center.

Demographic and baseline disease characteristic data will be summarized for each treatment group and consist of age, parity, cervical cytology and HPV status, prior treatment for vHSIL, prior treatment for cervical HSIL, smoking, and co-morbidities in which we focus on auto-immune diseases and history of cancer.

At each follow-up visit, the following data will be collected: visual/physical examination and preferably photo documentation of the vulva. If there is any suspicion of recurrence of vHSIL, a biopsy will be taken for histology and HPV typing endpoint, cervical cytology, and if additional treatment will be started.

At the start of the study, after 6, 24, and 60 months, patients will be asked to fill out questionnaires.

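### Optional gain: the primary model is valid but adjusts only for the stratification factors; prespecify age and smoking as well, and standardise to the announced relative risk

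*Protocol article*

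**What the plan says.** Under *Data analysis*, the protocol article announces a relative risk of recurrence within 24 months, estimated "using logistic regression methods adjusted for country of inclusion, treatment types, and primary versus recurrence vHSIL". The confidence interval is specified for the odds ratio, and significance comes from a likelihood ratio test.

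The three covariates are those used in the allocation. Under *Randomization, stratification, blinding and treatment allocation*: "Randomization will be stratified by country of inclusion, treatment group (surgery, laser vaporization, and topical imiquimod), and the first episode of vHSIL versus recurrence".

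*Data collection* lists the baseline data to be summarised by arm. They "consist of age, parity, cervical cytology and HPV status, prior treatment for vHSIL, prior treatment for cervical HSIL, smoking" and co-morbidities. Age and smoking are in that list but not in the primary model.

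*Sample size calculations* rests on "a recurrence rate of 19% versus 32% in favor of HPV vaccination" and states "With a target power of 0.8 and a two-sided alpha of 0.05". The total is 498 (249 per arm), "including a loss of follow-up and a 20% correction of the supposed different effect". It does not rely on covariate adjustment.

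**The concern.** In a logistic model, adjusting for a baseline variable that truly predicts the outcome raises the power of the treatment test. Stratification does not balance age or smoking. If one of them predicts recurrence, leaving it out gives up a little power and leaves a chance imbalance uncorrected.

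Two features make this worth a line here. The target power is only 80%, and *Background* describes the case-control study behind the planned effect as non-significant because its groups were small. And if extra covariates are not named in advance, a visible imbalance in smoking, say, invites argument about adjustment after unblinding.

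**Working it through.** **1. The planned sample size.** Inputs from *Sample size calculations*: 32% v 19%, two-sided alpha 0.05, power 0.80. Allocation is 1:1.

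n per arm = [1.96 × √(2 × 0.255 × 0.745) + 0.8416 × √(0.32 × 0.68 + 0.19 × 0.81)]² / 0.13² = (1.208 + 0.513)² / 0.0169 ≈ 175.3, so 176.

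With the 20% correction taken as a factor of 1.2: 176 × 1.2 = 211.2, so 212. With an assumed 15% loss to follow-up: 211.2 / 0.85 = 248.5, so 249 per arm and 498 in total. The article gives no loss rate, and other combinations also come close (for example 176 / 0.8 / 0.90 gives 490 in total). The stated 498 is therefore consistent with its inputs but cannot be strictly verified. The 212 evaluable per arm used below rests on this route.

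**2. Power and events before any covariate gain.** Power for 32% v 19% is 79.7% at 174 per arm, 86.9% at 212, 88.7% at 224 and 91.7% at 249. Expected events are 212 × (0.32 + 0.19) = 108, or 249 × 0.51 = 127. Either number supports two or three extra terms.

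**3. Power change from extra covariates.** Model: logit(risk) = a + t × arm + b × z, with z a standard normal baseline score. The values of a and t are solved so that marginal risks stay at 32% and 19%. The values of b are assumptions, because the article gives none. Both models are fitted to the same simulated trials, and the table shows the paired change in power of the likelihood ratio test at 212 per arm, in percentage points (Monte Carlo SE in brackets).

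| b (log OR per SD) | Base model without covariates; score plus two useless covariates added; 4,000 trials | Base model with stratification terms; 8,000 trials |
|---|---|---|
| 0 | 0.0 (0.2) | −0.2 (0.14) |
| 0.3 (AUC about 0.58) | +0.8 (0.2) | +0.6 (0.17) |
| 0.5 (AUC about 0.63) | +1.3 (0.3) | +1.3 (0.22) |
| 0.7 (AUC about 0.68) | +2.6 (0.4) | not run |

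The right-hand column is nearer to the planned model. It assumes 4 countries, 3 treatments and 2 episode types, all without effect. A further paired simulation against a stratification-adjusted base, at 212 and at 249 per arm, gave no loss at b = 0, about +0.5 for a weak score, +1 to +1.5 for a moderate one and about +2.5 for a stronger one.

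Under equal risks of 25.5%, the adjusted test kept its size: 5.0% at b = 0 and at b = 0.5.

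**4. Extremes.** At 174 per arm the change ran from about −0.4 points (useless covariate) to about +6 (b = 1.0, AUC about 0.74). At 249 per arm it ran from about 0 to +3. Nothing in the article supports a predictor as strong as b = 1.0.

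**5. What the gain is worth.** Power rises by 88.7 − 86.9 = 1.8 points between 212 and 224 per arm. By linear interpolation, +1.3 points equals about 12 × 1.3 / 1.8 ≈ 9 women per arm.

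**6. Chance imbalance.** For a covariate present in half the women, the SD of the difference between arms is √(2 × 0.25 / 212) = 0.049, or 4.9 points. A gap near 10 points would arise about one time in twenty.

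**The case against.** The strongest reply is that nothing here is wrong. Adjusting for the factors that stratified the randomisation is a valid primary analysis. A condensed article may leave further covariates to an analysis plan that is not shown. All of that stands, and it is why the point is optional. The article does name the covariate set, however, so adding to it is best done openly and before unblinding.

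A reader might infer that the plan gives away free power. The documents do not support that. They call no baseline variable prognostic, the gain is about zero if none is, and extra covariates carry some cost.

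A reader might also infer that the remaining baseline data serve only for description. That goes too far. HPV type is analysed under secondary objective 5 and cervical findings under objective 9, and prior vHSIL treatment probably overlaps heavily with the first-episode-versus-recurrence factor already in the model.

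HPV status is a doubtful candidate as it stands. *Data collection* lists it with cervical cytology and *Detailed procedure* obtains it alongside cytology, so it may be cervical or lesional. If lesional, simple positivity may vary little, because *Background* describes vHSIL as caused by high-risk HPV.

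Chance imbalance is ordinary randomisation variation that the confidence interval already reflects, and a fixed covariate list already makes later adjustment a visible departure. The imbalance argument is therefore secondary.

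Finally, the odds ratio is non-collapsible, so extra covariates change what it means. This is correct, and standardising to a marginal relative risk answers it.

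**Conclusion.** The planned primary model is valid, and the 498 does not depend on this point. Adding age and smoking is a minor, optional improvement. At 212 or 249 per arm it changes power by about 0 to +2.5 points for assumed strengths of 0 to 0.7 log odds ratio per SD, with essentially no loss if the covariates are not prognostic.

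The size rests on that assumed strength, on the planned 32% v 19%, and, for 212 per arm, on an assumed 15% loss. Larger gains need predictors stronger than anything the article documents. Standardising has a separate benefit: it yields the relative risk that *Data analysis* announces but for which it plans no interval.

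**What to change.** Before unblinding, state in the analysis section or the SAP that:

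- the primary logistic model includes age (continuous) and smoking beside the three stratification factors, with the treatment test still by likelihood ratio;
- missing baseline values are handled by a simple rule fixed in advance;
- HPV status is added only if it is first defined as cervical or lesional and blinded data show that it varies enough to be useful;
- the relative risk is obtained by standardisation: predict each randomised woman's risk under vaccine and under placebo from the fitted model, average each set over all women, and take the ratio with a 95% interval (delta method or bootstrap);
- the model with stratification factors only is reported as a sensitivity analysis.

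No new data and no extra patients are needed. The cost is the missing-value rule, the standardisation step and one added sensitivity analysis.
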